#### Dose Escalation

Dose escalation on the phase I portion of this study should not occur until a sufficient waiting period has occurred after patients have been treated. A period of 90 days must pass in order to assess toxicity. If 90 days have elapsed without DLT in each of the first seven (7) patients enrolled to a specific dose level, then dose escalation to the next level may proceed. Patients will continue to be enrolled to each dose level (up to a maximum of 15 patients) with ongoing assessment of those reaching 90 day follow-up so long as either criteria for defining the MTD or criteria for further dose escalation is not reached. If fifteen patients are enrolled to a given dose level yet criteria for adequate follow-up are not reached in a representative sample of patients, further enrollment to the protocol will be suspended until adequate follow-up is reached. The phase I portion of this study will be completed when either of the following events occurs: 1) the MTD for a given cohort is reached or 2) when the highest protocol dose level is completed and tolerated

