#### Phase I Dose Escalation

The phase I study is designed to end if the rate of DLTs within 90 days from the start of treatment is 33% or higher. For each dose level cohorts, a total of seven to fifteen patients will be enrolled. If zero out of the first seven with 90 day follow-up, two or fewer out of the first nine with 90 day follow-up, three or fewer out of the first twelve with 90 day follow-up, or four or fewer out of the first fifteen of patients with 90 day follow-up experience a DLT as defined above, then the dose will escalate to the next dose level. If three or more of the first nine patients, four or more of the first twelve, or five or more of the first fifteen patients experience a DLT, then the MTD will be considered to have been exceeded. The MTD will be defined as the immediately previous lower dose level tolerated.

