#### Phase I Waiting Periods

Dose escalation on the phase I portion of this study should not occur until a sufficient waiting period has occurred after patients have been treated. A period of 90 days must pass in order to assess toxicity. If 90 days have transpired without DLT in each of the first seven (7) patients enrolled to a specific dose level, then dose escalation to the next level may proceed. Patients will continue to be enrolled to each dose level (up to a maximum of 15 patients) with ongoing assessment of those reaching 90 day follow-up so long as either criteria for defining the MTD or criteria for further dose escalation is not reached. If fifteen patients are enrolled to a given dose level yet criteria for adequate follow-up are not reached in a representative sample of patients, further enrollment to the protocol will be suspended until adequate follow-up is reached.

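### The escalate and MTD-exceeded rules count different patients, so an early DLT without 90-day follow-up can trigger both on the same data

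*Protocol*

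**What the plan says.** The protocol states the set of patients behind the escalation decision in three ways.

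- **Section 4.1.1, Dose Escalation:** the next level may open when 90 days have elapsed "without DLT in each of the first seven (7) patients enrolled to a specific dose level". Section 10.1, Phase I Waiting Periods, has the same rule: "If 90 days have transpired without DLT in each of the first seven (7) patients enrolled to a specific dose level".
- **Section 10.1, Phase I Dose Escalation, escalate branch:** "If zero out of the first seven with 90 day follow-up, two or fewer out of the first nine with 90 day follow-up", then at most three of twelve and at most four of fifteen, again among patients with 90-day follow-up.
- **The same paragraph, MTD-exceeded branch:** "If three or more of the first nine patients, four or more of the first twelve", or five or more of the first fifteen. This branch has no follow-up condition.

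The paragraph opens by saying that the study is "designed to end if the rate of DLTs within 90 days from the start of treatment is 33% or higher". Section 7.4 gives no stopping rule of its own and refers to section 10.1. Enrolment goes on while follow-up matures, to at most 15 patients per level, as long as neither the MTD criteria nor the escalation criteria are met (Phase I Waiting Periods).

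Three other places bear on the point. Sections 4.2 and 6.1.1 make every treated subject evaluable for toxicity. Section 4.7 allows replacement only of a patient who did not receive the fraction. Under section 5.5.2, withdrawal of consent ends follow-up.

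**The concern.** A patient can have a DLT and then not reach day 90: she may withdraw consent, be lost to follow-up or die. A grade 5 toxicity definitely attributed to therapy is itself a DLT, and if death comes before day 90 she can never have 90-day follow-up. Taken literally, the escalate branch leaves her out and the MTD-exceeded branch counts her. Such exclusion is informative, because she is left out after having had the event being counted.

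The stake is the primary decision of the trial, which is also its stopping rule. With limits of 0/7 and 2/9, one patient can change the result. If both branches are met, the protocol directs escalation and also declares the MTD exceeded, and nothing says which governs.

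A smaller gap has the same origin. Because enrolment continues, 0/7 can be met while DLTs already seen in later patients at that level meet 4/12 or 5/15.

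**Working it through.** **1. The protocol's own figure.** 3/9 = 4/12 = 5/15 = 33.3%, so the MTD-exceeded boundaries match the stated 33%. The largest counts that still allow escalation are 2/9 = 22.2%, 3/12 = 25.0% and 4/15 = 26.7%.

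**2. A cohort that meets both branches.** Ten patients are treated. Three of the first nine have a DLT, one of those three is lost on day 30, and the tenth completes 90 days without a DLT.

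| Branch in section 10.1 | Patients counted | Count | Result |
|---|---|---|---|
| MTD exceeded | first nine | 3/9 | MTD exceeded |
| Escalate | first nine with 90-day follow-up (lost patient out, tenth in) | 2/9 | escalate |

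**3. How often this can happen.** Inputs:

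- True DLT rate p = 1/3, the protocol's threshold.
- f = share of DLT patients without 90-day follow-up. The protocol gives no figure; I assume 0.1 to 0.3.
- Patients without a DLT are assumed to complete 90 days.
- Enough patients are enrolled to fill nine places with follow-up.

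The DLT rate among patients with follow-up is q = p(1 − f)/(1 − pf). At nine patients, at most 2 and at least 3 cover every outcome, and 0/7 always leads to at most 2/9. P(X ≤ 2 | n = 9) is therefore the chance that the escalate branch is met.

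If the first nine treated have at most two DLTs, the first nine with follow-up also have at most two, because each DLT patient left out is replaced by one patient, who adds at most one DLT. So whenever the MTD-exceeded branch is not met, the escalate branch is. It follows that

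P(both met) = P(X ≤ 2 | 9, q) − P(X ≤ 2 | 9, p).

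| f | q | P(≤2/9) at q | P(≤2/9) at p | Both met |
|---|---|---|---|---|
| 0 | 0.333 | 37.7% | 37.7% | 0 |
| 0.1 | 0.310 | 43.6% | 37.7% | 5.8% |
| 0.2 | 0.286 | 50.1% | 37.7% | 12.4% |
| 0.3 | 0.259 | 57.5% | 37.7% | 19.8% |

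Entering the rate as 33% instead of 1/3 gives 38.5% at f = 0, and 44.4%, 51.0% and 58.3% for the three values of f.

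**4. What this does to the chance of clearing the level.** If the MTD-exceeded branch takes precedence, clearing requires at most two DLTs among the first nine treated, so the chance stays at 37.7% whatever f is. If the escalate branch takes precedence, it is the third column, about 44–58% over both entries of the rate.

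**5. Later DLTs alongside a clean 0/7.** With p = 1/3 and no loss, P(0/7) = (2/3)^7 = 0.0585. Meeting 4/12 then needs at least 4 DLTs in patients 8–12, probability 0.0453. Meeting 5/15 needs at least 5 in patients 8–15, probability 0.0879. Even adding the two without allowing for overlap gives 0.0585 × (0.0453 + 0.0879) = 0.0078, so this occurs in under 1% of cohorts.

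**The case against.** The strongest reply is that the follow-up wording is only a maturity condition: wait until the patients have been observed for 90 days, then count. Sections 4.2 and 6.1.1 make all treated patients evaluable for toxicity, and section 4.7 allows no replacement once the fraction has been given. That is probably the intent. These sections do not define the set for the escalation decision, however, and the paragraph that does puts the condition on one branch only.

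A reader might infer that the wording raises the chance of clearing a level with a 33% DLT rate from 38% to 44–57%, or that an early death on treatment would never count. The protocol does not support either inference. The MTD-exceeded branch still counts that patient, and the rise occurs only if escalation overrides a stopping criterion already met.

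A reader might also take the difference between enrolled and followed up at seven patients to change the outcome by itself. Mostly it does not. With one early DLT among the first seven and the other patients free of DLT so far, the level goes on to nine and the count there cannot exceed 2/9. Only the timing differs.

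Two further limits stand. The 10–30% loss is assumed; after a single fraction, with the 3-month check made by telephone and adverse events followed to resolution or stability, it may be lower. And the conflict needs patients beyond the ninth to be enrolled already, since the waiting-period text ends enrolment once the MTD criteria are met. Enrolment does continue during the 90 days, and reported DLTs must first be verified, so the overlap is possible but not certain.

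**Conclusion.** The concern holds as a contradiction in the primary decision rule. Sections 4.1.1 and 10.1 do not agree on whom to count, and within section 10.1 the two branches use different sets and can both be met. At a true DLT rate of 1/3 with 10–30% of DLT patients lacking 90-day follow-up, that happens in about 6–20% of cohorts. This figure assumes no loss among other patients and prompt enrolment beyond nine; slower enrolment or less loss would lower it. Any effect on the chance of clearing the level depends on a precedence that the protocol does not state. The conflict between 0/7 and DLTs in later patients is real but rare. As the protocol fixes these rules itself and section 7.4 relies on them, the point should not be left to the analysis plan.

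**What to change.** Reconcile section 4.1.1 and both parts of section 10.1 to one DLT-evaluable set, used for the escalate and the MTD-exceeded branches alike: every irradiated patient at the level who either had a DLT within 90 days or completed 90 days without one. State also that, before any escalation, all DLTs already observed at that level, including those in patients enrolled after the seventh, are checked against the MTD-exceeded boundaries.

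The definition also settles a case that the enrolled wording leaves open, namely a patient lost before day 90 without a DLT: she is not evaluable, and the next patient is counted.

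The cost is wording only. Occasionally one more patient must reach day 90, within the existing cap of 15 per level.

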#### **4.1.2 Cyberknife localization, simulation, immobilization**

Patients will be positioned supine in a stable position capable of allowing accurate reproducibility of the target position from treatment to treatment. Positions uncomfortable for the patient should be avoided so as to prevent uncontrolled movement during treatments. A variety of immobilization systems may be utilized including Vac Loc® bags, stereotactic frames that surround the patient on three

sides, and large rigid pillows. All positioning systems must be validated and accredited by the Study Committee (Principal Investigator and Institutional PIs) prior to enrolling or treating patients on this trial. Patient immobilization must be reliable enough to insure that the Clinical Target Volume (CTV) does not deviate beyond the confines of the Planning Treatment Volume (PTV)

Daily localization will also be achieved using a more direct method of localization of the target than conventional treatment (i.e., one that uses skin and bony landmarks solely as a surrogate to the target position). Fiducials are used help ensure accurate daily target localization prior to treatment. Special considerations must be made to account for the effect of internal organ motion (i.e., breathing, etc.) on target positioning and reproducibility. This will be achieved using the fiducial tracking, Excite® tracking, and/or Synchrony® real-time tracking associated with the Cyberknife® per established system standards. Paired low-energy X-ray sources generate orthogonal X-ray images to determine the location of fiducial markers or bony landmarks continuously throughout treatment

Computed Tomography will be the primary image platform for targeting and treatment planning. The planning CT scans must allow simultaneous view of the patient anatomy and fiducials used for targeting. Treatment planning images should be performed in the treatment position using the methods described above for patient immobilization. Axial acquisitions with gantry 0 degrees will be required with spacing  $\leq 3.0$  mm between scans. The CT scan should start at or above the mandible and extend several cm below the inframammary fold (including the entire lung). Images will be transferred to the treatment planning computers via direct lines, disc, or tape.

#### 4.1.3 **Gammapod breast cup placement, simulation, immobilization**

The breast immobilization cup device (**BCID**) will be supplied by Xcision. With the breast hanging prone (patient bent over at the waist), the patient's breast will be measured to determine the size of the inner cup. Once the appropriate cup site has been selected any gaps  $> 1$  cm will be filled with a silicone filler attached to the inner cup. The inner cup will then be fitted into the appropriate pink silicone flange as chosen by the physician. The appropriate outer cup with built in fiducial system will be selected (S, M, or L) and attached to the inner cup and flange. Medical adhesive spray will be applied to the flange.

With the immobilization device complete, the breast will then be placed into the the cup. A slight negative pressure will then be applied, fixed at approximately 150 mm Hg. The breast will then be immobilized in the cup. If the seal cannot be created with the vacuum pump, additional adhesive may be utilized and or tape applied. If the seal cannot still not be maintained, then the inner/outer cup sizes and/or silicone filler may be changed. This may occur several times until either the physician deems the attempts futile, the patient's skin becomes irritated from the adhesive and/or patient preference.

#### **CT-based treatment planning for the GammaPod Treatment**

Once the breast is properly immobilized, the patient will step onto the image loader and be rotated into the prone position. The breast cup will then be locked to the image loader table. Patients will then undergo CT simulation in the prone position. The CT scan will begin at the thyroid notch and extend to below the infra-mammary fold (including the entire lung) with a slice thickness of 1.0 mm throughout the breast.

If at the time of CT simulation the tumor is found to be located  $> 5$  mm above the table top (as seen in Figure 1), If the tumor is located above this area, the patient

will be deemed ineligible for the gammapod per treating physician and should proceed with cyberknife or MR LINAC treatment if possible. (Description of Gammapod breast cup placement, simulation, immobilization and figure below from [name] from University of Maryland)

[figure not shown]

Figure 1: the line where you see artifact indicates the line from which tumor should not extend > 5 mm.

### MR-LINAC Simulation and Immobilization

The MR-LINAC allows practitioners to obtain MRI images at simulation and use them during planning and delivery. Contrast will be given and functional imaging will also be available. Patients will be simulated in supine position, and breast immobilization may be used per treating physician.

#### 4.1.4 GTV, CTV, PTV Target Volumes for both Cyberknife and Gammapod

##### Target Volumes for Treatment

Gross Target volume (GTV): this will be defined as the tumor as delineated on CT images and the location of the biopsy clip. Care should be taken by the radiation oncologist to change the windowing to optimize the contouring windows. Information from the breast MRI should also be utilized to assist in contouring. If the RO is unsure of the contours, it is recommended that the institutional breast radiologist be available for discussion/assistance.

Clinical Target volume (CTV): the GTV will be equal to CTV as we are using a SBRT technique and the surrounding tissue will inherently be getting high doses of radiation from the dose fall off.

Planning Target volume (PTV): the PTV will be a recommended concentric expansion of the CTV of 3-10 mm excluded from the skin and chest wall. As imaging techniques improve and/or dose is escalated, the PTV margin may be reduced at the discretion of the treating physician. The PTV margin will take into account set up error, and imaging modality used for planning (ie; CT scan versus MRI for planning)

### **GTV, CTV, and PTV for MR LINAC treatments**

Gross Tumor Volume (GTV)- this will be defined as the tumor delineated on the MR images/CEM and/or contrast enhanced CT scan

Clinical Target Volume (CTV)- the GTV will be equal to CTV as we are using a SBRT technique and the surrounding tissue will inherently be getting high doses of radiation from the dose fall off.

Planning Target Volume (PTV): The PTV will be a concentric expansion of the CTV of anywhere between 3mm-10mm but recommended to be 5mm excluded from the skin and chest wall.

#### **4.1.5 Radiation Planning and Target Goals for MR LINAC, Gammapod and Cyberknife:**

- 95% of the PTV should receive a minimum of 27 Gy and 99% of the target volume (GTV) receives a minimum of 93% of the prescription dose. Minor deviation if 90% of PTV receives 27 Gy. All efforts should be made to meet the skin constraint even if PTV coverage will be compromised. In this situation, would prioritize skin, brachial plexus, and spinal cord constraint over PTV coverage and this is acceptable and not a deviation, and will not be deemed a protocol violation if PTV coverage not met in order to meet these OAR constraints. Efforts should be made to keep the PTV volume coverage to a minimum dose of 27 Gy to 95% of volume. In the situation when the GTV is close to skin, prioritize the skin constraint over GTV coverage.
- Max hot spot < 130% of the prescription dose is recommended
- Prescription will be either 30 Gy, 34 Gy, or 38 Gy to the GTV/CTV per appropriate dose cohort.

#### **Critical Organ Dose-Volume Limits**

The following table lists maximum dose limits to a point or volume within several critical organs. These are absolute limits, and treatment delivery that exceeds these limits will constitute a major protocol violation

In order to verify each of these limits, the organs must be contoured such that appropriate dose volume histograms can be generated. Instruction for the contouring of these organs will follow below. When all constraints cannot be met the following priority should be met:

Priority 1: Spinal cord, brachial plexus, skin, trachea, large and small bronchus  
 Priority 2: Cover PTV  
 Priority 3: Heart, rib, thyroid, lung

| Serial Tissue    | Volume | Volume Max (Gy) | Max Point Dose (Gy)** | Endpoint (≥Grade 3) |
|-------------------------|---------------|------------------------|------------------------------|----------------------------|
| Spinal Cord and medulla | <0.35 cc      | 10 Gy                  | 14 Gy                        | myelitis                   |
| Brachial Plexus         | <3 cc         | 13.6 Gy                | 16.4 Gy                      | neuropathy                 |

|                                       |                                       |                                      |                        |                            |
|---------------------------------------|---------------------------------------|--------------------------------------|------------------------|----------------------------|
| Heart                                 | <15 cc                                | 16 Gy                                | 22 Gy                  | pericarditis               |
| Trachea and Large Bronchus* (CK only) | <4 cc                                 | 17.4 Gy                              | 20.2 Gy                | stenosis/fistula           |
| Bronchus-smaller airways (CK only)    | <0.5 cc                               | 12.4 Gy                              | 13.3 Gy                | stenosis with atelectasis  |
| Rib                                   | <5 cc                                 | 28 Gy                                | 33 Gy                  | Pain or fracture           |
| Skin                                  | <10 cc                                | 25.5 Gy                              | 27.5 Gy                | ulceration                 |
| Parallel Tissue                | Critical Volume (cc)           | Critical Volume Dose Max (Gy) |                        | Endpoint (≥Grade 3) |
| Thyroid gland (CK only)               | 5 cc                                  | 15 Gy                                |                        | Hypothyroid                |
| Ipsilateral Breast                    | <40% of whole breast reference volume |                                      | ≥ 50% prescribed dose  | Cosmesis                   |
| Ipsilateral Breast                    | <20% of whole breast reference volume |                                      | ≥ 100% prescribed dose | Cosmesis                   |
| Mean Heart dose                       |                                       |                                      |                        | Please record value        |
| Lung (Right & Left) CK only           | 1500 cc                               | 7 Gy                                 |                        | Basic Lung Function        |
| Lung (Right & Left) CK only           | 1000 cc                               | 7.6 Gy                               | V-8Gy <37%             | Pneumonitis                |
| Chest Wall                            | <30cc                                 | 30 Gy                                |                        | Chest wall pain            |

\*Avoid circumferential irradiation

\*\* "point" defined as 0.035cc or less

### **Dosimetry Compliance**

Exceeding dosimetric limits by more than 2.5% constitutes a minor protocol violation. Exceeding dosimetric limits by more than 5% constitutes a major protocol violation.

#### **4.1.6 Cyberknife and MR LINAC Treatment Planning Goals**

##### **1) Normalization**

The treatment plan should be normalized such that 100% corresponds to the maximum point dose in the irradiation volume and is required to be within the CTV volume.

##### **2) Prescription Isodose Surface Coverage**

The ideal prescription isodose surface will be chosen such that 95% of the target volume (PTV) is covered by at least 27Gy and 99% of the target volume (GTV) receives a minimum of 93% of the prescription dose. Minor deviation prescription isodose coverage in the instance that other normal structure constraints need to be met, is 90% of the target volume (PTV) covered by 27Gy. All efforts should be made to meet the skin constraint even if PTV coverage will be compromised. In this situation, would prioritize skin, brachial plexus, and spinal cord constraint over PTV coverage and this is acceptable, and will not be deemed a protocol violation if PTV coverage not met in order to meet these OAR constraints. Efforts should be made to keep the PTV volume coverage to a minimum of dose of 27 Gy to 95% of volume.

In the situation when the GTV is close to skin, prioritize the skin constraint over GTV coverage.

- 3) Target Dose Heterogeneity  
The prescription isodose surface selected in number 2 (above) must be  $\geq 50\%$  of the dose at the maximal dose point or normalization point.
- 4) High Dose Spillage
  - a) Location  
Any dose greater than 105% of the prescription dose should occur primarily within the CTV itself and not within the normal tissues outside of the CTV. Therefore, the cumulative volume of all tissue outside of the CTV receiving a dose greater than 105% of prescription dose should be no more than 15% of the CTV volume.
  - b) Volume  
Conformality of CTV coverage will be judged such that the ratio of the volume of the prescription isodose meeting criteria 1) through 4) to the volume of the CTV is ideally less than 1.3.
- 5) Respect all critical organ dose-volume limits listed in Section below
- 6) Reduction of dose to ipsilateral breast: Based on the previously mentioned studies, cosmesis is dependent on dose to uninvolved ipsilateral normal breast. Thus, there will be strict guidelines reducing the dose to the whole breast volume so that  $<40\%$  of the whole breast reference volume receives  $\geq 50\%$  of the prescribed dose and  $< 20\%$  of the whole breast reference volume receives  $\geq 100\%$  of the prescribed dose.
- 7) Reduction of dose to the contralateral breast: The contralateral breast should be contoured and should receive  $<3\%$  of the prescribed dose to any point.

